### **11.3.6. Analysis of the secondary criteria**

The qualitative criteria will be compared between groups by the Chi-square, adjusted Chi-square or Fisher exact test, depending on the expected number of participants under the assumption of independence. Logistic regression models will be used to adjust the comparison for confounding factors where appropriate. The conditions of application of the regression models will be verified.

Quantitative criteria will be compared between groups by Student's t test or Wilcoxon test if the normality of the criterion is not verified. Transformations to normalize the criterion can be performed if necessary. Linear regression models will be used to adjust the comparison on confounding factors if necessary. The conditions of application of the regression models will be verified.

Concerning the imaging data, voxel-to-voxel analyses will be conducted using SPM software, either by using intergroup and intragroup comparison statistics (Two-sample T-test, Full Factorial Design, Flexible Factorial Design... to study differences between different groups at the same visit), and regression (Multiple regression, to study the impact of variables of interest on our measures), or by applying specific and elaborate methods for longitudinal analyses, for which the investigators have developed experience, before performing repeated measures ANOVA. Analyses in regions of interest can also be performed by extracting values (volume, perfusion, amyloid marking, etc.) from the brain maps obtained in the different imaging modalities in order to perform statistical analyses on specific regions.

All analyses will be adjusted for potential confounding factors, which will be identified for each analysis (e.g., age, education level, gender).

### **11.3.7. Other analysis**

The database will be frozen when 1/3, 2/3, and all participants are recruited in order to allow analyses that will be defined a priori in the statistical analysis plan. Additional analyses will be performed on the data acquired at inclusion with regard to the secondary objectives defined in the protocol.

Further analyses will be conducted by the investigators based on (i) the advancement of knowledge in this area and (ii) the results of the analyses that meet the primary and/or secondary objectives outlined above. For example, if a gender effect (male/female) is found on the effects of the intervention, post-hoc analyses will be conducted to better understand the mechanisms of these differential effects.

These analyses may be performed as data become available at the request of the investigators, after prior validation by the Scientific Council. They must be integrated in the statistical analysis plan of the trial.

A record of all tests performed will be maintained by the sponsor.

## **12. Communication**

### **12.1. Terms and conditions for the publication of results**

All data collected in the course of this research are the property of the sponsor and may not be disclosed to any third party without the written consent of the investigator.

The results are published in the form of scientific articles in peer-reviewed journals and presented at national and international conferences. Any publication or communication (oral or written) is decided by mutual agreement between the coordinating and principal investigators as well as the scientific managers and will respect the international recommendations: "Uniforms Requirements for Manuscripts Submitted to Biomedical Journals" (<http://www.cma.ca/publications/mwc/uniform.htm>).

All publications must follow the rules set out in the AVIESAN publication charter. The mention of the origin of the funding, the authorizations of the competent authorities, the consent of the participants must appear in the acknowledgements according to the model suggested below:   
\*/Ethics statement /\*/This study is part of clinical trial \*\*\*\*CXX-XX\*\* sponsored by Inserm. It was granted approval by local Ethics Committee or "Comité de Protection des Personnes" on ---\*\*\*\*DATE\*\*---, authorized by the French authorities (\*\*\*\*ANSM\*\* \*\*\*\*NB\*\*), and registered in a public trials registry (\*\*\*\*CT XXXX\*\*).

All participants gave their informed, written consent to participation, in line with French ethical guidelines.

The signatories of the publications are the people who actually participated in the elaboration of the protocol, its progress and the writing of the results. The executive committee of the European consortium "Medit-Ageing" (ExCom) has the task of deciding on the analyses and publications carried out as well as on the signatories of the publications resulting from this protocol.

### **12.2. Procedures for writing the final report**

The final report of the research will be written, in collaboration, by the coordinator and the biostatistician of this research. This report will be submitted to each of the investigators for review. Once a consensus has been reached, the final version must be endorsed by the signature of each investigator and sent to the sponsor as soon as possible after the research has been completed. A report written according to the reference plan of the competent authority must be sent to the competent authority and to the CPP within one year after the end of the research, understood as the last follow-up visit of the last participant included. This time limit is reduced to 90 days in the event of premature termination of the research.

### ***12.3. Procedures for informing participants about the overall results of the research***

Individuals who participated in the trial may, if they wish, be informed of the overall results of the research by the coordinating investigator after the research is completed.

Articles and abstracts from this study will be sent to participants who wish to receive them.

### ***12.4. Procedures for informing individuals about health data during and after research***

Individuals may be informed at any time of the health data concerning them, upon written request to the coordinating investigator.

Any clinically significant abnormality detected in the examination or test results will be communicated to the participant and the physician previously selected by the participant.

### ***12.5. Terms and conditions relating to press communication***

The articles and abstracts resulting from this study will be sent before publication to the executive committee of the European "Medit-Ageing" consortium (ExCom) where the Clinical Research Unit is represented and the Department of Scientific Information and Communication (DSIC) will also be kept informed.

## **13. Confidentiality**

### ***13.1. Terms of confidentiality with respect to the individuals***

The information required by the protocol will be collected in the eCRF and an explanation will be given for each missing data. Data will be completed in the eCRF as they are obtained whether they are clinical or para-clinical data. Pseudo-anonymization of participants will be ensured by an anonymization code on all documents required for the research. Computerized data on a file will be declared to the CNIL according to the procedure adapted to the case

### ***13.2. Terms of confidentiality with respect to the trial***

Access to clinical and source data will be direct in case of monitoring, audits commissioned by the sponsor, and/or inspections by competent administrative authorities.

## 14. Protection of persons

### 14.1. *Ethical rationale of the protocol*

**Anticipated benefits:** For the participants, there is a direct benefit to participating in this trial. They will benefit from very good care, from an in-depth follow-up over 18 months thanks to this protocol. For all the volunteers, they will contribute to improving the understanding of Alzheimer's disease and its early detection, the impact of life factors, the effects and mechanisms of mental training such as meditation or learning a foreign language on the mental health and well-being of the older adults.

#### **Predictable risks:**

Neuropsychological tests: they do not involve any risk to the participant.

MRI: as performed in this trial (i.e. without injection of contrast medium), MRI has no known risks; the only inconvenience is to have to lie down without moving the head during the examination.

PET Scan: exposure to ionizing radiation is low and does not present a significant risk (the estimated dosimetries are reported below). The main inconveniences are the insertion of a venous catheter and lying down without moving the head for about 20 minutes during the acquisition of images. Before each PET scan, renal and hepatic functions will be evaluated, and, in addition, a blood sugar control will be performed before the FDG-PET scan.

For Amyvid®: The probability of occurrence of cancer or hereditary abnormalities is low. No serious adverse events related to the administration of Amyvid® have been reported. The most frequently observed adverse events are headache (infrequent events are described in the Amyvid® Product Monograph).

For the FDG-PET:

For Glucotep®, exposure to ionizing radiation may induce cancer or the development of hereditary deficiencies. As the effective dose is 7.6 mSv for a maximum recommended activity of 400 MBq, the occurrence of these adverse effects is unlikely (see SPC).

Polysomnographic, Somno-Art® and actimetric recordings: these recordings present no risk to the participant.

#### **Dosimetry:**

The injected activity of Amyvid® is optimized and equal to 4 MBq/kg. The effective dose for Amyvid® is estimated to be 18.6 µSv/MBq (SPC data). The effective dose resulting from the administration of a 280 MBq dose of Amyvid® for a 70 kg adult is therefore less than 5.5 mSv. For an administered activity of 280 MBq, the dose delivered to the target organ (brain) is 2.8 mGy.

The effective dose of FDG is 0.019 mSv/MBq, i.e. here 3.80 mSv for an injected activity of 200 MBq. The dose absorbed by the bladder (critical organ) is 0.13 mGy/MBq, i.e. 26 mGy for 200 MBq injected (data according to the Glucotep® SPC).

The participant will be asked to hydrate and urinate approximately one hour before the start of the examination, and then immediately afterwards. These precautions allow us to reduce as much as possible the quantity of product present in the bladder and thus the irradiation of this organ. The duration of the examination is approximately 1h30 including the installation of the volunteer, the injection of the radiopharmaceutical and the acquisition of the images. The acquisition of the PET images lasts 10 minutes and then 20 minutes for the PET-Amyvid® and 10 minutes for the PET-F-FDG during which the participant must remain immobile, preceded by the acquisition of the X-ray scanner for the attenuation correction.

For the PET scan, the attenuation correction is made from an estimate of the attenuation map by X-ray scanner acquired according to a low dose protocol. The scanner acquisition field is limited to the brain, and includes the lens which (1) cannot be protected and (2) is mainly irradiated by scattered radiation. For the parameters used (120 kV, 10 mA, rotation time 0.5 s, pitch of 1.375, collimation: 4x3.75 mm), the effective dose and equivalent dose for the lens are respectively 0.038 mSv and 0.75 mSv for an examination.

The following summarizes the total effective radiation doses received by participants during the entire trial:

| Visits                               | PET Scan                 | Male (mSv)         | Female (mSv)       |
|--------------------------------------|--------------------------|--------------------|--------------------|
| Inclusion (V1)                       | PET-Amyvid®              | 5,32 + (2 x 0,038) | 5,32 + (2 x 0,038) |
|                                      | PET-  F-FDG | 3,80 + 0,038       | 3,80 + 0,038       |
| 18 months later (V3)                 | PET-Amyvid®              | 5,32 + (2 x 0,038) | 5,32 + (2 x 0,038) |
|                                      | PET-  F-FDG | 3,80 + 0,038       | 3,80 + 0,038       |
| 29 ± 6 months post-intervention (V4) | PET-  F-FDG | 3,80 + 0,038       | 3,80 + 0,038       |
| Total for the whole trial            |                          | 22,306             | 22,306             |

## 14.2. Ethical and regulatory provisions

The research will be carried out in compliance with the French regulations in force, in particular the provisions relating to biomedical research of the Public Health Code, article L 1121-1 and following, the Bioethics laws, the Data Protection Act, the Helsinki Declaration, as well as the Good Clinical Practices and the present protocol.

The investigator agrees to conduct the research in accordance with these ethical and regulatory provisions. They are aware that all documents and data relating to the research may be subject to audits and inspections carried out in compliance with professional secrecy and without any possibility of medical secrecy being invoked. The investigator acknowledges that the results of the research are the property of Inserm, the promoter of the research.

### **14.3. *Comité de Protection des Personnes (CPP)***

Before implementing the research, the sponsor will submit the project to the local CPP for its opinion and will provide it with all the necessary information (research protocol, data collection medium (adapt this term to the research - observation book, questionnaire, etc.), information and consent form, any other relevant document that must be presented to the Committee, etc.).

The trial cannot begin until Inserm has been informed of the unreserved favorable opinion issued by the CPP on the submitted protocol. This opinion will include the title and number of the protocol assigned by the sponsor, the documents examined, as well as the date of its examination and the list of CPP members who participated in it.

The sponsor will inform the CPP of all subsequent amendments and of all serious or unexpected adverse events and developments that arise during the course of the research and that are likely to affect the safety of the individuals involved, in accordance with the sponsor's procedures described in this protocol.

### **14.4. *Insurance and funding***

Inserm, as promoter, has taken out a civil liability insurance policy for the entire duration of the trial under the number (0100846414031-160021-10998), in accordance with French legal and regulatory provisions on biomedical research.

The Certificate of Insurance for this protocol is attached as annex 11.

Research funding is provided by the EU (H2020-PHC22-2015 program).

### **14.5. *Procedures for obtaining consent from individuals***

The written informed consent of all persons participating in the research must be obtained by the investigator, registered as a physician and declared as an investigator to the sponsor, prior to any act performed within the framework of the research protocol and regardless of the act performed, in accordance with the regulations.

The information will be given orally and in writing in the first part of the information and consent form (Annex 2). The information will be written in clear language, perfectly understandable for the

person. It must contain all the elements that the person must be informed of, in accordance with the Public Health Code, article L 1122-1.

The person's consent to participate in the research is collected in writing on the second part of the information and consent form. This second part must be written in clear language that is perfectly understandable to the person who is to undergo the research. It must contain all the elements to which the person consents. Consent is given by signing and writing the first name, surname and date in the handwriting of the person who is to undergo the research.

In addition, the investigator who collects the consent form dates and signs the form in the space provided and ensures that (1) the form is accurate and that there are no missing entries or dates, and (2) an original copy of this document is given to the participant. They keep a second original copy in a secure, access-controlled location.

The investigator should ensure that the person undergoing the research has had time to make a free decision and has read and understood the information and consent form.

The information and consent form is a document that will have been approved prior to the implementation of the research by the CPP, during the review of the protocol.

The participation of the persons to the present protocol will be registered on the national file of the persons lending themselves to a biomedical research, managed by the Ministry of Health. Indeed, the non-expert seniors participating in this research will receive an indemnity for the constraints suffered and in compensation for the travels carried out within the framework of this research up to 600€ at the inclusion, 200€ at intermediate, 800€ at the end of the intervention, and finally 500€ (if they accept the optional long-term follow-up) at the end of their participation in this research. The senior experts will receive a compensation of 550€ upon inclusion and will be reimbursed upon presentation of receipts for expenses related to their participation in this trial. This indemnity will be due to them in proportion to their participation in the research. It will be paid in full only if they participate in all the visits, examinations and tests planned by the research.

They are not allowed to participate simultaneously in any other research during a 12-month exclusion period.

For participants in the "passive control" group who wish to do so, it will be proposed to finance a 2-month MBSR (Mindfulness Based Stress Reduction) meditation course (2h/week for 8 weeks + 1 day) or an English course (module: 15h-20h), at the end of the trial. This internship must be completed within 6 months after the end of the interventions.

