## 3.3. Provisional schedule of the trial (Flow-Chart)

The projected schedule for the trial is illustrated in Figure 3 below:

Duration of recruitment:

- Non-expert seniors: recruitment will take place 3 months before the beginning of each inclusion wave, i.e. 9 months of recruitment.
- Expert meditators: recruitment will be done on an ongoing basis and over a total period of 73 months (until February 2022; due to an interruption in recruitment in 2020 and part of 2021 linked to COVID-19 and the resulting health measures).

Maximum duration of participation for each participant:

- Expert meditators: 6 months (Screening visit V0 + Inclusion visit V1)

And in the Age-Well substudy - Lockdown: 24 months (April 2020-April 2022)

- Non-expert seniors: 53±6 months (3 months for V0 + V1 + 18 months for intervention + 3 months for Follow-up Visit 3 + 29 months without intervention which is the long-term post-intervention visit (V4)) (± 6 months depending on health status changes and a possible new period of confinement). Total duration of data collection: 6 years (1st participant included in December 2016 and last follow-up of the last participant: in June 2022 ± 6 months depending on the evolution of the health situation and a possible new containment period).

And in the Age-Well substudy - Lockdown: 24 months (April 2020 - April 2022)

Total duration of the research: 7 years (6 years for data collection + 1 year for data analysis) as shown below:

[figure not shown]

Figure 3: Provisional schedule of the Age-Well trial (data collection and analysis).

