### **6.16.2. Defining the end of trial on individuals**

Once all the examinations have been completed, i.e. the V1 visit for expert meditators and the V1 to V4 visits for non-expert seniors, the trial will be completed for the participants (end of study for the participant).

The end of the trial will be defined as the end of the analyses, approximately 12 months after the last visit of the last included participant.

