### 11.2. *Calculation of the study size*

#### Study on non-expert seniors:

The comparison between the meditation group and the no-intervention group is going to focus on the difference in 1) volume and 2) perfusion of the anterior cingulate cortex 18 months after the start of the intervention compared to the value at inclusion, with an expected effect size of 0.75 (effect size of short-term meditation vs. no intervention, from a meta-analysis on the effects of meditation on brain imaging markers: Fox et al, 2014). Given that the intervention in the current protocol is 18 months, we consider that the effect size will be at least equal to 0.75.

The same effect size of 0.75 is expected for the comparison between the meditation group and the English learning group on the difference in 1) insula volume and 2) insula perfusion 18 months after the start of the intervention compared with the inclusion value.

To show an effect size of 0.75 for each comparison, with 80% power and a two-sided first-species risk of 1.25% (Bonferroni correction because four comparisons will be performed) 42 participants per group must be recruited for a total of 126 participants.

Assuming that the effect size assumptions are conservative and that precautions are taken at the time of recruitment to best ensure adherence of participants to the trial, we expect that the risk of dropout after knowledge of the randomization group is very low and that the power of the study is preserved. However, we will implement close monitoring of these refusals at the beginning of the trial. In order to increase the statistical power of the secondary analysis on the FDG-PET examination carried out from

the second wave of inclusion, 24 participants will be recruited in addition, i.e. 8 additional participants per group (meditation, English, passive control) for a total of 150 participants.

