#### **No intervention arm:**

No intervention will be delivered to participants assigned to this arm, during the study duration.

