### **Objective 3bis**

The difference between measures from partners' questionnaires obtained post-intervention (18 months) versus 29 mois +/- 6 mois months later (i.e. 29 mois +/- 6 mois months after the end of the intervention) will be compared between the three groups. (see Section “*Descriptive analysis*” above for comparative methods).

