**Objective 9 (WP 1 to 6)**

Comparison and correlations between measures at baseline, post-intervention (18 months) and 29 mois +/- 6 mois months after the end of the intervention in participants of the passive condition (control group) and participant' partners to identify the determinants of mental health and well-being in ageing, considering areas of cognition, psycho-affective/emotion, compassion, support, mindfulness, sleep, wellbeing and quality of life measures (and biological and radiological measures depending on budget availability).

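### The course funded for passive controls falls before V4 and is not barred from the V3 window, yet the SAPs describe the arm as untreated and Objectives 3bis and 9 do not plan for it

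*Combined protocol and SAP*

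**What the plan says.** Protocol 14.5 says of the passive controls that "it will be proposed to finance a 2-month MBSR (Mindfulness Based Stress Reduction) meditation course", with an English module of 15 to 20 hours as the alternative. The course is voluntary. It is placed at the end of the trial, but the next sentence sets a different clock: "This internship must be completed within 6 months after the end of the interventions".

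Other sections describe the same period differently:

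- Protocol 3.3 builds each senior's participation from "18 months for intervention + 3 months for Follow-up Visit 3 + 29 months without intervention", ending at V4.
- Protocol 6.11 sets V4 at 29±6 months after the intervention.
- Protocol 6.16.2: "The end of the trial will be defined as the end of the analyses", about 12 months after the last visit of the last participant.
- Both SAPs, under the no-intervention arm: "No intervention will be delivered to participants assigned to this arm, during the study duration".
- Protocol 6.8 asks participants to avoid the other arms' activities, but only while the intervention lasts.

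The control arm is used at V4 in two places in the secondary SAP. Under Objective 3bis, changes in partner questionnaires from V3 to V4 "will be compared between the three groups". Objective 9 uses measures at baseline, 18 months and V4 "in participants of the passive condition (control group) and participant' partners to identify the determinants of mental health" and well-being.

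**The concern.** MBSR belongs to the same class of intervention as the experimental arm, and the English module to the same class as the active control. A passive control who takes either one before a study visit is no longer an untreated comparator at that visit. Because the choice is the participant's own, exposure may be related to well-being and motivation. That matters most for Objective 9, whose outcome is well-being.

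Two things are at stake. At V4, the Objective 3bis contrast and the Objective 9 associations could be read as describing an untreated arm when some of its members have been trained. At V3, if any control finished MBSR before the scans, the meditation-versus-control contrast on the anterior cingulate (Objective 1) would be diluted. Section 11.2 takes its planning effect of 0.75 from the "effect size of short-term meditation vs. no intervention", and section 1.1.2 names the 8-week MBSR programme as the typical short programme. On the trial's own planning assumption, then, a short course cannot simply be dismissed as negligible.

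**Working it through.** **Timing relative to V4.** Months are counted from the end of a participant's own intervention period.

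- Latest scheduled completion of the course: month 6 (14.5).
- Earliest V4: 29 − 6 = month 23 (6.11).
- Gap: 23 − 6 = 17 months. Every course taken on schedule precedes V4.
- Least favourable reading of the deadline: the 6 months run from the end of the last wave. Three waves about 6 months apart (6.8) put the last wave 12 months after the first, so a wave-1 control finishes by 12 + 6 = month 18. This is still before month 23.

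**Timing relative to V3.**

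- V3 examinations are spread over 3 months after the intervention (3.3, 6.10).
- MBSR lasts 8 weeks: 56 / 30.4375 = 1.8 months.
- A course begun when the interventions end can therefore finish inside the V3 window. No section schedules this and no section forbids it, because the restriction in 6.8 has lapsed by then.

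**Which analyses use passive controls.**

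| Objective | Uses passive controls | Exposed to the problem |
|---|---|---|
| 1 (anterior cingulate, V1 to V3) | yes | only if a course precedes the V3 scans |
| 1bis (insula, V1 to V3) | no | no |
| 2bis, 2ter (V3 to V4) | no, the two intervention groups only | no |
| 3bis (partners, V3 to V4) | yes | yes, if any course is taken |
| 9 (baseline, V3, V4) | yes | yes, if any course is taken |

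**Reproducing the planned sample size.** Inputs from 11.2: d = 0.75, two-sided alpha 1.25%, power 80%. The two-sample noncentral t gives n = 41.24, rounded up to 42 per arm. This agrees with the protocol; power at 42 is 80.9%. At the 50 per arm now planned it is 88.3%.

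**Illustrative dilution of Objective 1.** Let u be the share of controls who finish MBSR before the V3 scans and f the share of the 0.75 SD effect they gain. The contrast becomes d = 0.75 × (1 − u × f). The documents give neither u nor f; both are assumptions.

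| u | f | d | Power, n = 42 | Power, n = 50 |
|---|---|---|---|---|
| 0 | – | 0.750 | 80.9% | 88.3% |
| 20% | 1 | 0.600 | 57.9% | 67.5% |
| 20% | 0.5 | 0.675 | 70.4% | 79.5% |
| 20% | 0.1 | 0.735 | 79.0% | 86.8% |

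The 10% row corresponds to relative class time: 8 × 2 = 16 h of weekly MBSR sessions against 18 × (52/12) × 2 = 156 h of weekly classes in the trial, and 16/156 = 10%. Contact time is only a rough guide to effect.

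**Does the per-protocol set already deal with it?** Both SAPs keep a passive control only if that person took neither meditation nor language classes, but they give no time limit. Read literally, a control who took MBSR after V3 could be dropped from the 18-month per-protocol analysis although the 18-month data are clean. For exploratory analyses unrelated to the intervention, the secondary SAP includes all participants, and the protocol (2.2.2) puts Objective 9 among the objectives not related to the interventions. For the other secondary analyses, the choice of strategy is left to the PI, validated by the ExCom.

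**The case against.** A reader might infer that the primary comparator is contaminated. The documents do not support that. No section schedules a course before V3. Section 14.5 itself calls the long-term follow-up optional, so its end of the trial can reasonably be read as the end of the core assessments, that is, after V3. If every control has V3 first, primary power is unchanged. Objective 1bis, half of the primary family, does not use this arm at all. The steepest power loss requires every counted control to choose MBSR over English, finish it before the scans and gain the full planned effect from about a tenth of the class time. These points stand, and they limit the primary-endpoint issue to a gap in wording.

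It can also be said that the SAPs already handle trained controls through the per-protocol sets, and that a practice questionnaire is given at V4 (protocol 6.11 and Table 6). Both exist. But the per-protocol rule has no time frame and need not reach Objective 9, and the questionnaire is not stated to capture course type or dates and is not tied to any control-arm analysis.

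Finally, protocol 6.8 limits the absence of intervention to the 18 months, which is consistent with a later course. That is so, but it leaves the broader statement in both SAPs, and the description of the period before V4 in 3.3, in contradiction with 14.5.

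**Conclusion.** The concern holds in a limited form. The two timings in 14.5 conflict under the trial's own definition of its end. Any course taken on schedule precedes V4 under every reading of the deadline, which contradicts the no-intervention statements in both SAPs and in protocol 3.3. Objectives 3bis and 9 then use an arm that may contain self-selected trained controls, with no planned handling. How far this alters their results cannot be quantified, because uptake is not stated; with no uptake there is no effect.

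For Objective 1 the exposure is possible but not shown. The power figures (about 58%, 70% and 79% against 81% at 42 per arm) illustrate 20% uptake before V3 under three assumed gains. They do not estimate what happened or will happen. The case for acting rests on the contradiction, the missing V4 handling and the low cost of repair, not on demonstrated harm to the primary result.

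**What to change.** 1. **Protocol 14.5:** reconcile the two timings and state that the course may start only after all of that participant's V3 examinations. This fits the existing deadline: 6 − 3 = 3 months remain, enough for an 8-week course. Align the wording of 3.3.
2. **eCRF:** record course type, dates and attendance for each passive control.
3. **Both SAPs, no-intervention arm:** limit the statement to the period up to V3.
4. **Secondary SAP, Objective 3bis:** keep all randomised controls in the main analysis and add a sensitivity analysis that identifies or excludes course-takers.
5. **Secondary SAP, Objective 9:** include course exposure between V3 and V4 as a covariate, with a sensitivity analysis in unexposed controls.
6. **Per-protocol definition, both SAPs:** apply the control-arm rule up to V3 for 18-month outcomes and up to V4 for long-term outcomes, so that a course after V3 does not remove clean 18-month data.

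The cost is wording changes, one eCRF page and a few secondary analyses. The incentive for controls is kept, though they may wait up to about 3 months for the course. The sensitivity subsets will be smaller and self-selected, which is why they should support the main analyses and not replace them.
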